### Statistical Considerations

It is anticipated that a sample size of 20 patients will be accrued to enable the investigator to deliver hemiablative seed BT with a reasonable amount of confidence. This feasibility study will proceed in 5 participating centers. Failure to accrue 15 patients in 24 months will initiate early closure of this study. The time-frame for completion of recruitment will be approximately 12 months, with a further 24 months required for collection of acute and late toxicity data, maturation of quality of life data, and correlation with the biopsy by 36 months.

We do not consider it necessary to use early stopping rules for poor quality implants (not adequate dosimetric parameters on day 30), or acute treatment-related toxicities because of the low number of patients we are aiming for. An analysis will be performed after 20 patients have participated in the study. Therefore, if greater than 20% of patients have poor quality implants, this procedure will be unacceptable.

Descriptive statistics will be used to describe the frequency at which prostatic cancer low grade disease can be seen on Mp-MRI, and the frequency of unilateral prostatic disease is found after a mapping of the prostate. In addition to standard PSA follow-up, response will be assessed by imaging at 20 and 36 months as well as by TRUS-guided biopsy at 36 months.

Data analysis will be undertaken by [name] with the assistance of a qualified statistician.

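### Four or fewer poor implants in 20 means only 'not shown to be unacceptable'; it does not demonstrate that the poor-implant rate is within the plan's 20% limit

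*Protocol article*

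**What the plan says.** Under Statistical Considerations, the protocol article justifies the sample size in one sentence: "It is anticipated that a sample size of 20 patients will be accrued to enable the investigator to deliver hemiablative seed BT" and so on, "with a reasonable amount of confidence". It gives no expected poor-implant rate, error rate or confidence level.

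The same section rules out interim looks at this outcome ("We do not consider it necessary to use early stopping rules for poor quality implants"), schedules a single look ("An analysis will be performed after 20 patients have participated in the study") and states the verdict: "if greater than 20% of patients have poor quality implants, this procedure will be unacceptable". A poor implant is one whose dosimetric parameters are inadequate at day 30. An accrual floor is also set: "Failure to accrue 15 patients in 24 months will initiate early closure of this study".

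Three other places bear on what a pass means. The primary objective (Trial Objectives, Textbox 1) is to demonstrate that hemigland delivery is feasible. Study Group describes the study as a pilot that comes before any commitment to a large trial. The Discussion defines success as feasibility shown by meeting the post-implant dosimetric parameters, after which the other outcomes are evaluated and a randomised trial can follow.

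**The concern.** This is the only numerical decision rule on the primary endpoint. It compares the observed proportion in 20 patients with 20% and makes no allowance for sampling error. Failing the rule has a stated meaning: the procedure is unacceptable. Passing has none of its own, but the objective and the Discussion supply one, namely that feasibility has been demonstrated. With 20 patients, a result that just passes is compatible with a true poor-implant rate of about twice the limit. If the plan is followed as written, the primary conclusion can claim more than the data support, and that conclusion is one of the inputs to the later randomised trial.

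**Working it through.** **Inputs.** From Statistical Considerations: n = 20, one analysis, unacceptable if more than 20% are poor. Since 0.20 × 20 = 4, the rule fails at 5 or more and passes at 4 or fewer. The document gives nothing from which n = 20 could be derived, so only the cut-off and its consequences can be checked.

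**Assumption.** Each implant is poor or not poor, independently, with a common true rate p. Then X, the number poor, is binomial(20, p).

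**1. Chance of passing**

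P(pass) = P(X ≤ 4) = Σ (k = 0 to 4) C(20, k) p^k (1 − p)^(20 − k).

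- At p = 0.25: 0.0032 + 0.0211 + 0.0669 + 0.1339 + 0.1897 = 0.415.
- At p = 0.30: 0.0008 + 0.0068 + 0.0278 + 0.0716 + 0.1304 = 0.237 from the rounded terms, 0.2375 unrounded.

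| True poor-implant rate | P(pass), n = 20 |
|---|---|
| 5% | 99.7% |
| 10% | 95.7% |
| 15% | 83.0% |
| 20% | 63.0% |
| 25% | 41.5% |
| 30% | 23.8% |
| 35% | 11.8% |
| 40% | 5.1% |

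The chance of passing falls to 10% only at a true rate of about 36%, and to 5% only at about 40%.

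**2. What the worst passing result shows**

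For 4/20 the exact (Clopper-Pearson) limits are:

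- lower two-sided 95% limit, from P(X ≥ 4 | p) = 0.025: p = 5.7%
- upper two-sided 95% limit, from P(X ≤ 4 | p) = 0.025: p = 43.7%
- one-sided 95% upper bound, from P(X ≤ 4 | p) = 0.05: p = 40.1%

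**3. Which passing results exclude 20%**

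The one-sided 95% upper bound for x poor implants solves P(X ≤ x | p) = 0.05. For x = 0 this is 1 − 0.05^(1/20) = 13.9%.

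| Observed poor | One-sided 95% upper bound | Excludes 20%? |
|---|---|---|
| 0/20 | 13.9% | yes |
| 1/20 | 21.6% | no |
| 2/20 | 28.3% | no |
| 3/20 | 34.4% | no |
| 4/20 | 40.1% | no |

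**4. Sensitivity to accrual**

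If only 15 patients were analysed (the accrual floor; 0.20 × 15 = 3, so pass at 3 or fewer), P(pass) would be 46.1% at a true rate of 25% and 29.7% at 30%. The one-sided 95% upper bound at 3/15 would be 44.0%.

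**The case against.** The strongest defence is that the rule is a one-sided failure screen in a pilot. It says when the procedure is unacceptable and states no hypothesis about a true rate. As a screen it behaves sensibly: a technique with a true rate of 10% passes in 95.7% of trials, and one with 40% fails in about 95%. Study Group explains the small size by difficult recruitment, and a pilot need not meet confirmatory error rates. All of this stands. It does not license the step from not failing to having demonstrated feasibility, which the objective and the Discussion take.

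A second defence is that exact intervals and operating characteristics are often left to a fuller document that is not shown. That is fair as to reporting detail. The point here is the rule and the meaning given to a pass, both of which this document fixes.

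The documents do not support four stronger readings that a reader might infer:

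- *That the rule wrongly passes 63% of the time at its limit.* The rule condemns rates greater than 20%, so a true rate of exactly 20% is not unacceptable under it. The 63% is only the limiting value just above 20%. The 25% and 30% rows are the clear false passes.
- *That a promised statistical confidence is not delivered.* The wording "to enable the investigator to deliver hemiablative seed BT with a reasonable amount of confidence" concerns delivering the treatment and has no number attached. It is a loose justification of the sample size, not a broken numerical promise.
- *That a false pass by itself launches the randomised trial.* The Discussion first requires toxicity, quality of life and local control to be evaluated, and Follow-Up Schedule ties the start to a median of 3 years' follow-up with biopsy results. The dosimetric rule is one of several conditions.
- *That 0 or 1 poor implants in 20 would establish feasibility.* At one-sided 95%, 1/20 does not exclude 20% (upper bound 21.6%). Accepting it means choosing a one-sided 90% level (upper bound 18.1%), which the protocol does not state. With that zone, a technique with an assumed true rate of 10% would score 0–1 in 39.2% of trials and 2–4 in 95.7% − 39.2% = 56.5%, so more than half of trials would be inconclusive.

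**Conclusion.** The concern holds as a fault in what a pass is taken to show. The cut-off is calculated consistently with the stated 20%, and n = 20 is not miscalculated, because no error rates were set for it to meet. The rule reliably rejects only techniques with true poor-implant rates near 40%. It passes a true rate of 25% in 41% of trials and 30% in 24%. A result of 4/20 leaves rates up to 40.1% (one-sided 95%) or 43.7% (two-sided 95%) open. A pass therefore cannot be read as evidence that the rate is within the plan's own limit, except at 0/20.

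The figures rest on exact binomial calculation with independent implants and a common rate across the 5 centres. If results cluster by centre, the real uncertainty would be larger. The 95% confidence level is the reviewer's convention, as the protocol states none.

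**What to change.** Keep n = 20 and the failure cut, and reword Statistical Considerations as follows:

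1. Five or more poor implants in 20: unacceptable, as now.
2. Four or fewer: 'not shown to be unacceptable', and not described as feasibility demonstrated. Report the observed rate with its exact upper confidence bound.
3. Claim that the poor-implant rate is below 20% only if that bound excludes 20%. At one-sided 95% this requires 0/20. If another level is preferred, fix it in advance.
4. Replace "with a reasonable amount of confidence" with the operating characteristics: P(pass) of 95.7%, 41%, 24% and 5% at true rates of 10%, 25%, 30% and 40%.
5. Align the primary objective and the Discussion with item 2.

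This changes wording only and needs no more patients. The cost is a less favourable claim. The chance of 0/20 is (1 − p)^20, which is 35.8% at an assumed true rate of 5% and 12.2% at 10%. Most passing results would therefore support only 'not shown to be unacceptable', even for a good technique.

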### Resources and Implementation

#### Ethics

The application for the South Eastern Sydney Local Health District (SESLHD) Human Research Ethics Committee has been recently approved.

#### Skills and Resources

Three of the investigators are experienced BT proceduralists with extensive experience in the use of TRUS and transperineal needle implantation. The fourth investigator is a BT fellow in training and will be assisting with the procedure.

Planning systems will be institution-dependant but must allow appropriate collection of the above mentioned data. Acceptable planning systems will include Variseed, Nucletron First, PSID, and MIM Symphony. TGA-approved iodine-125 seeds may be purchased from any of the vendors within Australia.

#### Data Collection

The necessary data to be collected at various time-points of the study is outlined in Figure 4. The principal and co-investigators will be responsible for collection of this data. This data will be manually entered onto paper forms and transferred to a secure database which is password protected and accessible only to the investigators.

#### Budget and Funding

The investigations beyond normal practice that are required for this protocol are (1) two TTGM biopsies of the prostate, one pretreatment and another one at 36 months following treatment; and (2) Mp-MRI of the prostate, required at baseline and again 20 and 36 months following completion of treatment to assess response.

The post-implant quality assessment will require a a non-Mp prostatic MRI at day 30. This is not our standard practice but we arrange it sometimes for specific patients that require more accurate post-implant quality evaluation. Apart from the 20 month and 36 month assessments, follow-up after completion of treatment is standard. The costs entailed by the MRI examinations and the TTGM prostate biopsy will be billed to the Internal Hospital Research Budget. Internal funding prior to commencement will be undertaken by each institution. SGCCC has already coordinated local funding using trust fund cost centre number and hence can proceed immediately after ethics approval. A grant application will cover part of the expenses. There will be no out-of-pocket cost for the patients enrolled in the study.

## Discussion

This protocol is designed to show feasibility in delivering hemigland focal therapy with seed BT. Our whole-prostate seed BT program has been running for more than 10 years with excellent results (data not published). We believe that our well-established experience with seed BT will ease the performance of the hemigland technique. The reduction in toxicity can be of significant importance, particularly in a well-selected population, therefore we consider the pre-implant investigations crucial.

If the trial is successful, showing feasibility meeting the dosimetric parameters in the post-implant setting, toxicity parameters, quality of life, and tumor local control will be evaluated. Once evaluated we will be able to move towards a RCT scenario comparing standard WG seed implant versus hemigland to confirm the benefit in toxicity and quality of life with the highest level of evidence. Cost effective analysis should be performed in the future given the cost of the pre-implant investigations before establishing the focal therapy technique.

Furthermore, this protocol will give us opportunities to study more data, such as the correlation between Mp-MRI findings with TTGMB which is still in early stages [64,65].

## Appendix

Multimedia Appendix 1 Quality of life instruments: Expanded Prostate Cancer Index Composite (EPIC) questionnaire, International Prostate Symptoms Score (IPSS) questionnaire, International Index Erectile Function (IIEF) questionnaire.

## Abbreviations

AS: active surveillance
BT: brachytherapy
CT: computed tomography
CTV: clinical target volume
ED: erectile dysfunction
HDRI: high dynamic range imaging
IIEF: International Index of Erectile Function
IPSS: International Prostate Symptom Score
LDR: low dose rate
Mp-MRI: multi-parametric-magnetic resonance imaging
MR-CT fusion: magnetic resonance imaging computed tomography fusion
MRI: magnetic resonance imaging
PAR: post-anesthesia recovery
PI-RADS 4: Prostate Imaging Recording and Data System Score 4
PI-RADS 5: Prostate Imaging Recording and Data System Score 5
PSA: prostate-specific antigen
PTV: planning target volume
RCT: randomized controlled trial
STGCCC: St George Cancer Care Centre
TRUS: transrectal ultrasound
TTGM: transperineal template-guided mapping
UF: ultra-focal
WG: whole gland
